# Impact of a shared decision-making mHealth tool on caregivers’ team situational awareness, communication effectiveness, and performance during pediatric cardiopulmonary resuscitation: study protocol of a cluster randomized controlled trial

**DOI:** 10.1186/s13063-021-05170-3

**Published:** 2021-04-13

**Keywords:** Situation awareness, Teamwork, Taskwork, Leadership, Mobile device, Information technology, Cardiopulmonary resuscitation, Pediatrics

## Abstract

**Background:**

Effective team communication, coordination, and situational awareness (SA) by team members are critical components to deliver optimal cardiopulmonary resuscitation (CPR). Complexity of care during CPR, involvement of numerous providers, miscommunication, and other exogenous factors can all contribute to negatively influencing patient care, thus jeopardizing survival. We aim to investigate whether an mHealth supportive tool (the Interconnected and Focused Mobile Apps on patient Care Environment [InterFACE]) developed as a collaborative platform to support CPR providers in real-time and share patient-centered information would increase SA during pediatric CPR.

**Methods:**

We will conduct a prospective, cluster randomized controlled trial by groups of 6 participants in a tertiary pediatric emergency department (33,000 consultations/year) with pediatric physicians and nurses. We will compare the impact of the InterFACE tool with conventional communication methods on SA and effective team communication during a standardized pediatric in-hospital cardiac arrest and a polytrauma high-fidelity simulations. Forty-eight participants will be randomized (1:1) to consecutively perform two 20-min video-recorded scenarios using either the mHealth tool or conventional methods. The primary endpoint is the SA score, measured with the Situation Awareness Global Assessment Technique (SAGAT) instrument. Enrollment will start in late 2020 and data analysis in early 2021. We anticipate that the intervention will be completed by early 2021 and study results will be submitted in mid 2021 for publication.

**Discussion:**

This clinical trial will assess the impact of a collaborative mHealth tool on increasing situational awareness and effective team communication during in-hospital pediatric resuscitation. As research in this area is scarce, the results generated by this study may become of paramount importance in improving the care of children receiving in-hospital CPR, in the era of increasing communication technology.

**Trial registration:**

ClinicalTrials.gov NCT04464603. Registered on 9 July 2020.

**Supplementary Information:**

The online version contains supplementary material available at 10.1186/s13063-021-05170-3.

## Background

Despite advances in resuscitation science and improvement of cardiac arrest (CA) survival over the past decades, only approximately 38% of children survive to hospital discharge after pediatric in-hospital cardiac arrest (p-IHCA). This number decreases to 6% to 20% after out-of-hospital cardiac arrest (p-OHCA) due to a non-traumatic cause [1, 2]. Survival after traumatic p-OHCA is even worse, with only 0.3% of children surviving to discharge with an intact neurological status [3]. Optimal technical skills influencing CPR quality are emphasized in resuscitation guidelines [4–8]. The American Heart Association (AHA) also highlights the importance of a team-based structure to optimize the management of critically ill patients to increase their chances of survival after cardiac arrest [9, 10]. However, the use of a team-based structure in critical situations does not ensure team performance and does not improve patient outcomes [11]. While rescuers have to assume individually assigned tasks, they should share a common and congruent goal-directed mental model. This implies effective non-technical cognitive and social skills to deliver optimal care, such as task management and coordination, team dynamics, leadership, SA, communication, and decision-making [9, 12–18]. Among these skills, SA and communication play a pivotal role.

SA refers to the individual’s ability to quickly gather pertinent information from the environment, unequivocal comprehension of its meaning, and the ability to project future events based on this comprehension [19]. This makes SA the main precursor to decision-making [20]. This concept can be extended to all team members, whereby each team member possesses complementary or shared SA required for their respective roles [21]. Poor SA during CPR can lead team members to be unaware of relevant information regarding the patient’s health clinical status, its implications, and the anticipation of patient requirements. This can impede the coordinated execution of CPR, impact on quality of care, increase the likelihood of errors and affect patient outcome [22, 23].

Effective, closed-loop, directed communication and information-sharing between team members is also essential during CPR. However, several disruptive factors can hinder their implementation, such as a noisy environment, interruptions, exogenous distractors, and the number of providers involved in various tasks [12]. A previous study demonstrated that ineffective communication among team members in critical care situations occurs in one-half of all events due to inaudible information or misunderstanding [15]. Moreover, non-team-leader-initiated communication (i.e., “outer-loop” communication) was observed in almost one-half of exchanges during CPRs, being potentially distracting for the team-leader and representing a lost source of information [24]. Hence, communication breakdowns and degradation of information-sharing are often attributable causes for adverse events and medical errors and also associated with degradation in SA [25]. This can directly impact morbidity and mortality [17, 26].

Current AHA resuscitation guidelines do not yet include specific recommendations to optimize non-technical skills during CPR. Similarly, in the Advanced Trauma Life Support (ATLS) course, there is little guidance on effective leadership, teamwork, or effective communication as a trauma team leader [27]. This partly relies on logistic barriers that make controlled and reproducible measurement of team interaction in real life-threatening trauma and cardiac arrest challenging [22, 28]. To overcome these limitations, in situ simulation-based studies offer the opportunity to assess non-technical skills in a standardized and controlled critical environment. Although previous organizational and training measures have been identified as possible means to improve team communication and SA during CPR [28–32], evidence is scarce regarding the impact of mobile health (mHealth) tools to support cardiac arrest team members. We developed a shared decision-making mHealth supportive tool (Interconnected and Focused mobile Applications on patients’ Care Environment [InterFACE]) as a collaborative platform to support CPR providers in real-time with shared patient-centered information.

### Previous work justifying this trial

InterFACE consists of a dual, interconnected mHealth tool composed primarily of a mobile device app, namely “Guiding Pad”, interfaced to a remote large liquid crystal display (LCD) screen installed in the resuscitation bay and situated above the patient’s head (Fig. 1). In a previous multicenter, randomized crossover trial [33], we showed that medication errors, time-to-drug preparation, and time-to-drug delivery for continuous infusions during simulation-based, pediatric, in-hospital post-cardiac arrest scenarios were significantly reduced using the drug-dosing app PedAMINES, embedded into InterFACE. In another recent randomized trial [34], use of the “Guiding Pad” mobile app was associated with a shorter time to first and subsequent defibrillation attempts, reduced intravenous medication and defibrillation dose errors, and improved adherence to AHA recommendations compared with the use of pediatric advanced life support (PALS) pocket cards. However, it remains to be determined whether the implementation of the entire mHealth tool during pediatric CPR would improve SA, leadership, team communication, and performance. In this cluster randomized controlled trial, we will explore this assumption in a simulated model.

**Fig. 1 Fig1:**
[figure not shown]
The InterFACE mHealth tool to be used during the forthcoming trial. The “Guiding Pad” mobile app installed on a tablet is communicating in real-time patient-centered resuscitation steps on the remote TV screen in the shock room. Informed consent for publication was obtained from the individuals (or their parent/legal) in Fig. 1

## Methods/design

### Objectives

The primary aim of this study is to investigate whether the mHealth tool improves SA among team members during standardized, high-fidelity p-IHCA and life-threatening polytrauma simulations. Secondary outcomes are the mHealth tool effect on leadership, team communication effectiveness, and performance compared with conventional communication methods. Our hypothesis is that the use of the tool might improve the above-mentioned non-technical skills, as well as clinical skills, when used by in-hospital emergency teams.

### Trial design and setting

This is a prospective, single-center, cluster randomized controlled trial that will be conducted in a tertiary pediatric emergency department (approximately 33,000 consultations/year) with voluntary pediatric emergency fellows, residents, and nurses. We will compare SA, leadership, communication skills, and team performance using the shared mHealth supportive tool (“InterFACE”, group A) or conventional team interactions (group B) during standardized p-IHCA and life-threatening polytrauma simulations. Participants allocated to group A will not be allowed to use any other cognitive support. Participants allocated to group B will be allowed to use the PALS pocket reference cards and a conventional calculator, but not any other cognitive support or mobile device app. No changes will be made to the app during the study.

The development of the study protocol followed the Standard Protocol Items: Recommendations for Interventional Trials (SPIRIT) 2013 Checklist (Additional file 1) [35]. Figure 2 shows the trial flow chart and Table 1 the trial schedule. This trial protocol version 1.0 received a declaration of no objection by the Geneva Cantonal Ethics Committee on March 18, 2020, as the purpose of the study will be to examine the effect of the intervention on healthcare providers. The trial will be conducted according to the principles of the Declaration of Helsinki [36] and Good Clinical Practice guidelines [37].

**Fig. 2 Fig2:**
[figure not shown]
Trial flow chart

**Table 1 Tab1:** Standard Protocol Items: Recommendations for Interventional Trials checklist (SPIRIT) Figure. (T) SAGAT, (team) situational awareness global assessment technique; RTLE, resuscitation team leader evaluation; TEAM, team emergency assessment measure; SUS, system usability scale

	Study period				
	Pre-enrolment	Enrollment/consent	Pre-study baseline/allocation	2 × 20-min scenario	Close-out
Timepoint	***–t***_***2***_	***–t***_***1***_	0	t_**1**_	t_**x**_
**Enrollment**					
**Invitation to participate**	X				
**Eligibility screen**		X			
**Informed consent form**		X			
**InterFACE 15-min learning session**			X		
**Allocation**			X		
**Intervention**					
**Group A (mHealth tool)**				X	
**Group B (conventional method)**				X	
**Assessments**					
**Demographic data**			X		
**(T)SAGAT**				X	
**RTLE (leadership)**					X
**TEAM (teamwork, communication)**					X
**Time to 2nd outcomes**				X	
**Medication/defibrillation errors**				X	
**3-item termination questionnaire (10-point Likert scale)**					X
**SUS questionnaire**					X

### Participants and eligibility criteria

Any physician performing a pediatric emergency medicine fellowship in the pediatric emergency department (PED), as well as any postgraduate residents pursuing a < 5 years residency in pediatrics at Geneva University Hospitals (Geneva, Switzerland), will be eligible. Registered nurses with a specialty in pediatric emergency nursing will be eligible. Inclusion criteria are having followed a standardized 15-min introductory course on the use of the InterFACE tool and being willing to grant written informed consent. Participation to a simulation in the past month is an exclusion criterion to avoid a recent training effect (knowing that in our PED, nurses, and physicians participate in about one simulation every 3 months).

### Informed consent process

On the day of participation, in the presence of the study investigators, participants will provide written informed consent. Important concepts will be highlighted via bulleted text. A checkbox will assess whether participants understand key consent information. These consent forms will be collected and countersigned by the study investigators and stored securely in a locked room at the University Hospitals of Geneva. If the study investigators have reason to believe that a participant is not aware of study requirements or may be unable to provide informed consent, they will notify the participant that they will not be enrolled.

### Recruitment process

To achieve adequate subject enrolment to reach the target sample size on the day of participation, teams will be randomly recruited and scheduled weeks before the start of the study by a blinded non-investigator. To avoid preparation bias, they will be informed of the upcoming simulation study, but not of its purpose and outcomes. In the case of participant unavailability, the research team will organize a replacement. As basic life support training is a requirement for caregivers at our institution, all participants will have previously completed this course prior to study entry. All nurses will be assumed to have an equivalent competence with intravenous drug preparation and dose calculation as this is part of their regular practice and training background. Study participants will not be involved in the study design, choice of outcome measures, or the execution of the study. No participant will be asked for advice on the interpretation or writing of the study results. All participants will be informed of the results after study completion.

### The InterFACE tool

InterFACE was developed at the Geneva University Hospitals following an iterative user-centered process and ergonomic-driven approach by senior pediatric emergency physicians and nurses, computer scientists, software developers, and ergonomists with a strong background in medical app development. On the basis of pediatric resuscitation observations, AHA and ATLS guidelines, and focus groups, the team worked closely together to identify the key functionalities and processes to be implemented [38]. Both main components—the “Guiding Pad” app and the remote screen—are part of the whole shared decision-making tool intended to support and guide CPR providers during resuscitation, while improving team SA.

The “Guiding Pad” app was developed using Angular version 8, a development framework created by Google to build mobile and web apps. Assessment of this app and details regarding its functionalities have been described in a previous randomized trial [34]. In brief, the app displays a split screen with PALS algorithms split into interactive stages and adapted for tablet devices, as well as patient-centered cognitive aids to help with real-time decision-making (Fig. 3). The user can easily navigate through the algorithm in use and across the multiple algorithms at any time. For the purpose of the trial, no specific trauma guidelines will be implemented within the app. Indeed, the ATLS guidelines follow substantially the same didactic approach as outlined in the AHA guidelines for patients with primary cardiac arrest, with specific attention given to the technical support of vital functions with trauma-related equipment. Therefore, the app allows to select an exhaustive pre-defined and organized list of resuscitation materials and trauma-related equipment (and also symptoms and conditions that can be encountered during CPR). Finally, weight-based drug doses are automatically calculated by an on-board engine inherited from another evidence-based app [33].

**Fig. 3 Fig3:**
[figure not shown]
“Guiding Pad” screenshots. Two screenshot examples of the Guiding Pad app. The left-hand side of the screen displays the AHA pediatric advanced life support (PALS) ventricular fibrillation (VF) and pulseless ventricular tachycardia (pVT) cardiac arrest algorithm. The current step (e.g., determining the shockable status of the arrhythmia) of the resuscitation process is surrounded by a blinking red line. Past actions already accomplished are shown as shaded. At the top right-hand side of the screen, a color-coded title depicts the current step in progress. On the right-hand side of the screen, the sequence of actions to be taken (e.g., to select the right pulseless dysrhythmias under consideration [left screenshot]) are displayed in a stepwise manner to facilitate accurate progression along the algorithm. The current action (e.g., to resume compression and ventilation [right screenshot]) is brought to the attention of the provider by a red-box warning and requires validation by a simple click. Once completed, the next action will be to deliver the weight-based epinephrine dose automatically calculated by the app and then to prepare amiodarone). At the bottom right-hand side, a footer helps to anticipate the next cardiopulmonary resuscitation step. CPR: cardiopulmonary resuscitation; IO: intraosseous; IV: intravenous; PEA: pulseless electrical activity

All critical actions performed by the team are automatically validated on the mobile app and reported on a remote LCD screen above the patient’s head in real-time via a dedicated and secured internal WiFi connection (Fig. 1). The pertinent information gathered through the mobile app, as well as the patient monitor, is therefore displayed in the sight of the entire resuscitation team to be shared in an easy-to-read and spatially organized manner, sorted in chronological order, and paralleling the CPR in progress (Fig. 4). According to the concept of the proximity compatibility principle to display design [39], information relevant to a particular resuscitation task is rendered close together within a dedicated window. All actions undertaken by the providers are saved in log files and can be retrieved at any time for debriefing or medical chart documentation purposes. Finally, the app’s architecture is flexible enough to accommodate additional information sources as future needs arise.

**Fig. 4 Fig4:**
[figure not shown]
InterFACE screenshot of the integrated LCD screen display. The information is displayed in windows that can be flexibly arranged in different layout positions and sizes around the screen, according to user preference. Each window contains patient-centered real-time information, displayed in chronological order and following the systematic ABCDE approach, including vital signs, identified pathology, interventions (procedures, medication received, etc.), as well as resuscitation algorithms. The first section on the left-hand side of the screen displays an entire algorithm overview, thus allowing users to situate the stepwise resuscitation progress in real time along that algorithm. The current step of the resuscitation process is surrounded by a blinking red line that allows an immediate understanding of the current position within the algorithm. Each action already performed turns gray. However, the tool provides the possibility for users to navigate back and forth through the algorithm (or other algorithms) at any time in order to select one of the resuscitation steps if needed. The right-hand side of the screen displays a detailed and clickable list of drug doses and equipment size at user’s disposal and intended as cognitive aids helping with decision making

### Intervention and resuscitation scenarios

Each team will comprise six participants: (1) a team leader (fellow in pediatric emergency medicine), (2) a physician (resident in pediatrics) undertaking the primary/secondary surveys and performing the procedures, (3) a dedicated trained assistant for airway management, (4) a dedicated trained assistant for chest compressions, (5) a nurse for vascular access and drug preparation/administration, and (6) a scribe (second nurse) to document events and actions in a chronological fashion (either with the app or conventional methods). As PALS instructors and senior physicians, the study investigators will not interfere in the conduct of the CPR (except in the case of a significant deviation from the algorithm that must be followed to achieve ROSC; which will then be regarded as an error). Among them, a study investigator will play the role of on-call hospital specialists and radiologists, if needed. A second study investigator will operate the simulator and a third will freeze the situation at certain defined timepoints and provide the scripted questions.

On the day of participation, each subject will complete an anonymous survey about basic demographic information, professional length of medical training, PALS and ATLS training, and simulation and computer experience. After random allocation, each team will receive: (1) a standardized 15-min training session on how to use the app, (2) a presentation of the simulation manikin’s characteristics, and (3) the topics of three assessment questionnaires (see below), but to prevent unblinding, not the queries themselves. The teams will then be asked to consecutively perform two 20-min highly realistic, scripted CPR scenarios on a high-fidelity WiFi manikin (Laerdal SimBaby, Laerdal Medical, Stavanger, Norway). High levels of realism are known to immerse participants in the simulated experience and prevent confounding variables that might potentially affect the way they perform [30]. Within each scenario, three separate “freeze” periods will occur at random points in time to assess the shared and complementary SA of each team member individually regarding the CPR in progress. During freezes, the entire team will have to turn away from the patient, monitors and app to “blank out” the simulator and avoid any cognitive help from the simulated environment that could otherwise bias the respondent’s answers to the questionnaires. The scenarios will be standardized to strictly follow the 2018 AHA pediatric ventricular fibrillation algorithms [5] (Fig. 5) and the 2018 ATLS guidelines [40]. They will be extensively tested before the trial to achieve optimum functioning on the day of participation and performed on the same high-fidelity manikin already primed with vital signs appropriate for the scenarios. Both scenarios will be completed in the same order and the procedure will be standardized across all teams to follow the same chronological progression and range of difficulty in order to ensure that each participant is exposed to exactly the same case, with similar challenges in technical and non-technical skills. The uniform delivery of the scenarios throughout the entire study will minimize confounders. Study investigators will allow progression through the scenarios only once predefined milestones have been reached, irrespective of error occurrence or the time taken to achieve them.

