**Fig. 5 Fig5:**
[figure not shown]
AHA pediatric cardiac arrest algorithm – 2018 update [5]

The scenarios will be conducted in situ in the PED resuscitation bay to increase realism, thus allowing participants to make use of real resources in the actual environment where they are expected to perform CPR. The decision to use or not use any equipment will remain personal, as in real-life situations. All participants in group B will be offered the possibility to hold PALS pocket reference cards in their hands throughout the entire scenarios. Whether they refer to these or not will be left to their entire discretion, similar to real-life settings. The locale will be exclusively devoted to the simulation to prevent unexpected interruptions or external stimuli. Monitoring alarms will be activated to increase realism and stress, and distracting exogenous factors (telephone call, immediate unavailability of specialists, non-essential information, etc.) will occur.

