Practically, each scenario will be frozen three times (2-min duration per freeze; queries’ length will be compatible with time constraints) at random points in time during the scenario to issue queries chosen randomly from a predefined list (Additional file 3). Random freezes have been shown not to impact on participant performance measures [46] and to limit recall bias that could otherwise arise if queries are asked at the end of the simulation [21]. This will allow to assess respondents’ awareness of the current situation so that query occurrence will not be associated with the occurrence of specific related events [46]. During each freeze, participants will be asked to complete a total of eight multiple choice queries for level 1, four for level 2, and four for level 3 of SA in a written confidential manner. We will therefore collect per scenario a total of 768 SAGAT queries and eight TSAGAT, with a range of possible scores of 0 to 16 on each SAGAT questionnaire and a combined total score of 0 to 96 on TSAGAT. Over the course of the experiment, this will represent a total of 96 SAGAT (768 queries) and 16 TSAGAT. No freezes will occur earlier than 5 min after the beginning of the scenario to allow participants to build up a representation of the situation [46]. The second and third freezes will be interspaced at least 1 min from each other and from the first freeze.

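### The freeze rule blanks group A's only aid but not group B's hand-held PALS cards, so the arms may answer the primary SAGAT queries under unequal conditions

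*Protocol article*

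**What the plan says.** All places are in the protocol article.

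- **Primary endpoint** (Abstract, Methods): "The primary endpoint is the SA score, measured with the Situation Awareness Global Assessment Technique (SAGAT) instrument". Under Primary outcome, Situational awareness, the queries are answered in writing during three 2-minute freezes per scenario. The mix is "eight multiple choice queries for level 1, four for level 2, and four for level 3 of SA", so 16 items.
- **Freeze rule** (Intervention and resuscitation scenarios): "During freezes, the entire team will have to turn away from the patient, monitors and app". The stated purpose is to "avoid any cognitive help from the simulated environment that could otherwise bias the respondent’s answers to the questionnaires".
- **Group A's aids** (Trial design and setting): "Participants allocated to group A will not be allowed to use any other cognitive support".
- **Group B's aids** (same section): "Participants allocated to group B will be allowed to use the PALS pocket reference cards and a conventional calculator". The text after Fig. 5 adds: "All participants in group B will be offered the possibility to hold PALS pocket reference cards in their hands throughout the entire scenarios". Whether they look at the cards is left to them.
- **Scribe** (Intervention and resuscitation scenarios): one of the six members records events, with the app in group A and by conventional methods in group B. What happens to that record at a freeze is not stated.

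**The concern.** A SAGAT score is comparable between arms only if both arms answer with the same help, or with none. The freeze rule names three things to turn away from. One is group A's sole permitted aid; none is an aid of group B. Turning away works for a manikin, a monitor or a wall screen, but it does not remove a card held in the hand. The only text on when cards may be held sets no limit at freezes.

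The cards and the app overlap in content. The InterFACE display shows the resuscitation algorithm and drug doses, and the protocol treats sight of the app as help to be blanked. The first scenario follows the AHA pediatric ventricular fibrillation algorithm, which belongs to the PALS material that the cards serve. An algorithm in hand could plausibly help with some queries on what the situation means or what comes next.

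Any such help would go to one arm only and would therefore be confounded with allocation, so no analysis could separate it from the effect of the tool. If investigators improvise at the freeze, practice may also differ between the eight teams.

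**Working it through.** **1. The passages side by side**

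| Item | Group A at a freeze | Group B at a freeze |
|---|---|---|
| Patient, monitors | turned away from | turned away from |
| App | turned away from | not used |
| PALS cards | not allowed at any time | may be held throughout; no exception for freezes |
| Calculator | not allowed | allowed; freezes not mentioned |
| Scribe's record | in the app | conventional methods; handling not stated |

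The Situational awareness section places the freezes during the scenario. A permission covering the whole scenario therefore covers them, unless another sentence takes them out. No sentence does.

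**2. Which queries could be affected**

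A generic card cannot show this patient's current state, so the 8 perception items should be largely untouched. At most the 4 comprehension and 4 projection items are open to it, 8 of 16. The query list is in an additional file that is not shown, so this is an upper limit by assumption. The second scenario is polytrauma managed under ATLS, where PALS cards should help less.

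**3. The plan's own sample size, as a yardstick**

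Inputs (Power and sample size calculation): difference 0.25, SD 0.2, two-sided 5%, power 90%, ICC 0.05, teams of 6.

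- n per arm = 2 × [0.2 × (1.960 + 1.282) / 0.25]² = 13.45, rounded up to 14. This reproduces the plan's 14.
- The plan raises this to 18 per arm. Design effect 1 + 0.05 × 5 = 1.25; 36 × 1.25 = 45, rounded up to 48. This also reproduces.

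**4. Illustration of what look-up could cost**

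Effective n per arm = 24 / 1.25 = 19.2. Standard error of the difference = 0.2 × √(2/19.2) = 0.0645. Power = Φ[(0.25 − b)/0.0645 − 1.960], where b is the rise in group B's mean score: b = (share of queries affected) × (gain in probability of a correct answer). The gains of 0.2 and 0.5 are assumptions, applied as if every group B member used the cards in both scenarios.

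| Queries affected | Assumed gain | b | Difference left | Power |
|---|---|---|---|---|
| none | – | 0 | 0.25 | 97% |
| 4 of 16 | 0.2 | 0.05 | 0.20 | 87% |
| 8 of 16 | 0.2 | 0.10 | 0.15 | 64% |
| 4 of 16 | 0.5 | 0.125 | 0.125 | 49% |
| 8 of 16 | 0.5 | 0.25 | 0 | 2.5% |

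The last row is the extreme end of the assumed range. If the cards help only in the cardiac arrest scenario, each b halves: 0.10 becomes 0.05 (87%) and 0.125 becomes 0.0625 (83%). If only some members look at the cards, b shrinks in proportion.

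A written record usable by the scribe alone, one member in six, lifting the 8 perception items by 0.2 to 0.5, gives b = 0.5 × 0.2 / 6 = 0.017 to 0.5 × 0.5 / 6 = 0.042, with power 95% to 90%.

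**The case against.** The best defence is the purpose clause. It applies to the entire team, in both arms, and reading a card while answering would defeat it. The list of items also looks like shorthand: it does not separately name the large InterFACE display, which surely must be out of view too. An investigator runs each freeze and could collect the cards. The sentence on holding cards describes care in progress, and Data collection and management deducts freeze time from scenario duration, so freezes might be read as outside the scenario. No sentence allows cards to be consulted while queries are answered. A fuller freeze script may sit in the complete protocol.

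Much of this stands as evidence of intent, but it does not settle the wording. The purpose clause speaks of help from the simulated environment, and the only act prescribed is turning away, which leaves a hand-held card where it is. Deducting freeze time corrects the timed outcomes and does not govern what may be held. The cards sentence is the more specific text, and staff following it would leave the cards in place.

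Two further points stand in full. To use a card on a projection query, a participant must know where the team is in the algorithm, which is itself situational awareness. And the bias would run against the tool, so it could not produce a false positive in its favour.

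**Conclusion.** The blanking rule is not symmetric for the primary endpoint. Read literally, group B may hold and consult an algorithm reference while answering SAGAT queries and group A may not. The result is a risk of bias against the tool, mainly on comprehension and projection queries in the cardiac arrest scenario. Its size is unknown: it depends on the query list, the content of the cards and how many members look at them, none of which the article gives. The power figures in the working rest on assumed gains and show only that the plausible range runs from negligible to serious.

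Three stronger readings may tempt a reader and are not supported:

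- **That SAGAT tests memory in one arm and look-up in the other.** Both arms lose sight of patient and monitors, and a generic card cannot answer questions about this patient's state.
- **That group B keeps a readable scribe's log at freezes.** The article says only that conventional methods are used and is silent on freezes. The point rests on the cards alone.
- **That the primary comparison is shown to be biased by a known amount.** The text creates the opportunity; it does not show that anyone would use it.

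**What to change.** Amend the freeze rule in Intervention and resuscitation scenarios to say that at every freeze, in both arms, the tablet, display, pocket cards, calculator and any written record are put out of sight before the query sheets are handed out, and are returned at restart. In the text after Fig. 5, qualify the permission to hold cards with: except during freezes. The two sentences then agree with each other and with the stated purpose.

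The cost is a few seconds at each of six freezes per team. An investigator is already assigned to run the freezes, and freeze time is already deducted from the timed outcomes. No extra staff or participants are needed. The change has to be in place before the first session, because the scores cannot be repaired afterwards. For any session already run, the video recordings could be checked for cards in hand at the freezes, and the finding reported with the primary result.
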